## Abstract

**Background::**

Chronic low back pain (CLBP) is 1 of the common clinical diseases, and many treatment methods can only improve the symptoms of pain in the short term. Traditional Chinese sports - Baduanjin has been proven to have a positive effect on chronic low back pain. However, the quality of the research is low, the sample size is small, and safety observations are lacking. We describe the protocol of a randomized controlled trial to study the efficacy and safety of Baduanjin chronic low back pain.

**Methods::**

This randomized, controlled, evaluator-blind, two-arm, parallel clinical trial will include 90 outpatients with chronic low back pain recruited from the First Hospital of Nanping City, Fujian Province. The patients were randomly assigned to the intervention group (Baduanjin exercise training) and the control group (not receiving any special exercise training) at a ratio of 1:1. Patients in the intervention group will receive Baduanjin exercise training 3 times a week for 24 weeks. The 2 groups received a 4- week follow-up observation at 24 weeks. The main result from the intervention before intervention to 24 weeks later, and the follow-up of 4 changes the visual analog scale score at weeks, and by independent t are tested groups. It will also review the Pain-related disability index, The Quebec Back Pain Disability Scale, Health-related quality of life, Roland Morris (Roland Morris) Disability Questionnaire, Overall Perceived Effect (OPE) and safety Compare. Cost data for cost-benefit and cost-benefit analysis will be collected.

**Discussion::**

This will be the first study to compare the effectiveness and safety of Baduanjin for patients with chronic low back pain. The results may help healthcare professionals make clinical decisions and may reduce the cost of treatment for this disease.

**Trial registration::**

ChiCTR2000033908

## Introduction

1

With the changes in human living environment and working conditions, Low Back Pain has become 1 of the most common public health problems in the world.^[1]^ Epidemiological surveys show that the point prevalence of low back pain is about 18%, and the lifetime prevalence is about 40%.^[2]^ Although many people's low back pain will recover within a year, more than 5% to 10% of patients will have persistent low back pain.^[3,4]^ When this kind of low back pain lasts for more than 3 months, it develops into a disease---Chronic Low Back Pain (CLBP).^[1,5]^ The dysfunction of low back pain caused by CLBP has different degrees of negative impact on patients’ mobility, daily function, work ability and quality of life,^[6–8]^ and is also the most common cause of disability among people aged 45 to 85.^[3,9]^ At the same time, it causes great burden to the patient's individual, family and social economy.^[10]^ Since the vast majority of low back pain patients are non-specific pain, the underlying pathological or harmful factors have not yet been identified.^[11]^ Although the evaluation and treatment methods have improved, the management of low back pain is still a challenge for researchers and clinicians.

Many clinical practice guidelines recommend various methods to evaluate and manage CLBP.^[12–14]^ These guidelines all mention the prudent use of imaging evaluations, pain medications, spinal injections, and surgical procedures.^[15]^ Unfortunately, these therapies are not always effective and may increase some adverse reactions, including nausea, vomiting, insomnia, headaches and disability. Other recommended management methods, including self-management, restorative activities and exercise, are considered effective methods.^[14,15]^ However, a unified management model has not yet been formed,^[16]^ and there are large differences in practice in different countries and regions. Although exercise has been recognized as a moderately effective method for the treatment of CLBP,^[17,18]^ there is limited data on the cost-effectiveness of some exercise treatments, which require expensive specialized equipment.

Baduanjin is a traditional Chinese way of exercise, which consists of 8n simple, independent and smooth movements.^[19]^ Although the results of each movement may be different, in general Baduanjin can promote the coordination of mind and body, thus regulating respiration and playing an important role in health care.^[19,20]^ In recent years, Chinese medicine has received more and more attention from scientific research circles, especially its benefits to human body and mental health.^[21]^ Baduanjin has been proven to be safe and effective,^[22]^ it can improve the physical condition of patients, such as reducing the symptoms of Low Back Pain, enhancing physical function, and reducing self- reported disability.^[23]^ In general, it can actively adjust various psychological indicators, such as anxiety, irritability, depression and concentration.^[24]^ In China, Baduanjin is a commonly used and widely used treatment method to relieve the symptoms of lower back pain, with relatively remarkable effect.^[23]^ It mainly through strengthening the back chest abdominal muscles and bones, adjust the cervical spine thoracic lumbar physiological curvature, to reduce the pain of patients.^[25–27]^ At present, the effectiveness of Baduanjin in the intervention of CLBP has been confirmed by previous randomized controlled trials,^[23,28]^ but these studies have some problems, such as small sample size, simple observation indicators and lack of safety observation.

Here, we describe the protocol of a randomized controlled clinical trial to evaluate the efficacy of Baduanjin intervention for CLBP. We plan to analyze the effectiveness and safety of Baduanjin interventions in terms of pain intensity, disability level, quality of life, and overall impression change through a 24-week exercise program to provide health practitioners with a low-cost and safe way to address this health issue.

## Materials and methods

2

### Objectives

2.1

The main objective of this study was to evaluate the effects of Baduanjin on back function in patients with low back pain, including pain intensity, disability level, quality of life, overall impression change, and safety outcomes.

### Research design

2.2

This study is a randomized, controlled clinical trials, will conform to the conditions of 90 participants according to the proportion of 1:1 were randomly divided into intervention group (Baduanjin group) and control group (not exercise training group). All the members of the intervention group received Baduanjin training 3 times a week for 24 weeks. All cases in the control group did not receive any exercise training for 24 weeks. Primary and secondary outcomes will be measured at baseline, 8, 16 and 24 weeks after intervention, and the next 4 weeks. The research design flowchart is shown (Fig. 1). The research protocol was described in accordance with “ SPIRIT 2013 statement: defining standard protocol items for clinical trials ”.^[29]^

**Figure 1 F1:**
[figure not shown]
Study design.

### Inclusion criteria

2.3

1.Male and female subjects aged 19 to 70 years;2.Pain that lasts at least 3 months;3.At the time of inclusion, pain and discomfort were over 40 mm on the 100 mm Visual Analog Scale (VAS);^[30]^4.Normal intelligence, able to communicate and communicate, able to complete the basic movements of Baduanjin;5.Voluntarily provide written informed consent and are willing to follow instructions related to the trial.

### Exclusion criteria

2.4

1.Suspected or confirmed severe spinal pathology (spinal fracture, metastatic, inflammatory or infectious disease, cauda equina syndrome, diffuse neurological disease);2.Nerve root injury (the same strength as the nerve root, the effect of sensation or reflex);3.Past medical procedures, including spinal surgery;4.The current medical condition plans to undergo major surgery during treatment;5.Be pregnant, breastfeeding, plan to become pregnant or refuse to use appropriate contraceptive methods during the trial period;6.Pain in places other than the waist is more severe;7.Participating in rehabilitation training and exercise therapy influencing the outcome of the trial within the last 2 weeks;8.It is up to the clinical trial investigator to judge whether the trial is qualified.

### Subject withdrawal criteria

2.5

1.Violate the inclusion criteria or meet the exclusion criteria;2.Serious adverse events hindered the continuation of the trial;3.Withdraw the consent of the subject or legal representative;4.Do not receive the entire course of treatment continuously;5.The investigator or subject violates the clinical trial protocol;6.Use of drugs or treatments that may affect the results of clinical trials without the permission of the researcher;7.The researcher believes that the progress is inappropriate.

### Recruitment

2.6

Recruiting patients from the Rehabilitation Department of the First Hospital of Nanping City, Fujian Province seeking treatment for CLBP, the trial began in October 2020 and the last follow-up is expected to be conducted in November 2023.

People who may meet the conditions will be screened first to determine their eligibility based on inclusion and exclusion criteria. Qualified personnel will receive data about the trial, and 2 well-trained research assistants will have an in-depth discussion of the provided information. Participants will be asked to sign a written informed consent form, after which a baseline assessment will be conducted.

Patient and public participation in the trial is currently in the recruitment phase. No patients and the public participated in this test.

### Sample size calculation

2.7

Perform sample size calculations to determine the appropriate number of participants. The main outcome will be the change of VAS score between the intervention group and the control group from before the intervention to the end of the last intervention. As far as we know, a previous clinical trial evaluated the effects of Baduanjin and conventional rehabilitation intervention for 8 weeks.^[28]^ The change of VAS score after treatment group (8^th^ week) was 2.37 ± 1.7 in the treatment group and 3.70 ± 1.39 in the control group. The following indicators will be considered: α = 0.05, statistical power of 95%, and follow-up loss of up to 20%. We use G∗POWER 3.1.9.7 (http://stats.idre.ucla.edu/other/gpower/) to calculate that the sample size of this study is 45 patients per group. Therefore, a total of 90 participants are required.

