### Outcome indicators

2.16

#### 
Primary endpoint

2.16.1

The main outcome of our study will be the change in VAS score of pain from baseline to the completion of the intervention (week 24).^[30]^ Patients will quantify pain intensity by marking the most relevant points anchored by 2 descriptors on a 100 mm horizontal line: 100 for ”most imaginable pain” and 0 for ”no pain”.

#### 
Secondary ending

2.16.2

Pain-related disability index is used to measure general disability related to pain.

The Pain Disability Index is a widely used and researched tool for measuring pain-related disability, especially in chronic low back pain, fibromyalgia, cancer, or chronic generalized pain.^[33]^ Pain Disability Index is mainly composed of 7 projects, including family responsibilities, entertainment, social activities, occupation, sexual behavior, self-care, and life support activities. Each item is evaluated using a numerical score scale of 0 to 10, where 0 means no disability, 10 means the highest disability, and the total score is 70 points. The higher the score, the more the pain interferes with daily activities. Pain Disability Index is easy to understand and is an effective and reliable tool.

The Quebec back pain disability scale is used to measure disability related to specific back pain.^[34]^

The Quebec back pain disability scale is mainly used to assess the difficulty of various daily activities patients with low back pain. These activities are mainly divided into 6 areas, across a total of 20 questions: bed rest (question 1–3), sitting (question 4–6), walking (question 7–9), exercise (question 10–12), bending over (question 13–16) and carrying heavy objects (questions 17–20). Each question has 6 options, with a score of 0 to 5. A score of 0 means no difficulty, a score of 5 means unable to complete, and a higher score means more severe dysfunction. The total score is 100 points.

Measure the health-related quality of life through the SF-36 Health Survey.^[35]^

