Our research has many advantages. First of all, All Baduanjin are personally guided by professional teachers of more than 5 years to improve the quality of experimental data. Second, we will not only assess pain intensity, but also clinical relevance, quality of life, level of disability, and overall assessment. Third, the intervention effect of each recorded time point was analyzed statistically, build a hybrid linear model, to provide basic data for the treatment course and training frequency of Baduanjin. Fourth, economic evaluation is included for the first time to provide data for the urban benefit of Baduanjin. Fifth, safety index evaluation is included for the first time to verify the safety of Baduanjin training. However, our research also has some limitations. First of all, our sample size calculation may be overestimated. According to previous study, the duration of treatment was only 8 weeks, while ours was 24 weeks. Secondly, the control group used in the study is different from ours, which may affect the results of the study. Finally, the daily activity of the patients in the control group could not be quantified. After the inclusion of the patients, we could only see those with significantly increased or decreased daily activity, and carried out elimination management, but we could not make quantitative comparison with the patients in the intervention group.

Despite its limitations, the results of this trial are expected to provide evidence for the efficacy, safety and economic benefits of Baduanjin in the treatment of chronic low back pain. To provide medical staff, medical staff and patients with long-term exercise therapy plan recommendations.

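### The VAS planning values are labelled as changes but then favour control; if they are really week-8 scores, the stated 95% power is not established for the change endpoint

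*Protocol article*

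**What the plan says.** Section 2.7 (Sample size calculation) names the quantity to be powered: "The main outcome will be the change of VAS score between the intervention group and the control group". Section 2.16.1 agrees, defining the primary endpoint as the "change in VAS score of pain from baseline to the completion of the intervention (week 24") on a 100 mm line where 0 is no pain and 100 is the worst.

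The planning values come from one earlier 8-week trial. They are introduced with "The change of VAS score after treatment group (8^th^ week") and given as follows: the change "was 2.37 ± 1.7 in the treatment group and 3.70 ± 1.39 in the control group". The other inputs are "α = 0.05, statistical power of 95%, and follow-up loss of up to 20" per cent. Section 2.2 sets 1:1 allocation. The result is 45 per group, 90 in total. No baseline mean or SD, SD of change, or correlation between baseline and follow-up is given.

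The Discussion lists as a limitation that "our sample size calculation may be overestimated". Its reasons are that the source trial ran for 8 weeks rather than 24 and used a different control group.

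**The concern.** Two things do not fit together.

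First, direction. In a pain trial a positive VAS change is normally read as a reduction. On that reading control improved by 3.70 and Baduanjin by only 2.37. The one piece of evidence behind the sample size would then run against the hypothesis. It would also run against the Introduction, which cites the same source among the trials said to confirm that Baduanjin works. A two-sided calculation uses only the absolute difference, so the software would not have exposed this.

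Second, the SD. The reading that restores the expected direction without moving the arms is that 2.37 and 3.70 are pain scores at week 8. Then 1.7 and 1.39 are SDs of a score. The endpoint is a change, and its SD depends also on the baseline SD and the correlation.

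At stake is whether a reader can rely on the stated 95% power for the declared endpoint. The limitation in the Discussion mentions neither matter.

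**Working it through.** **Inputs.** Means 2.37 and 3.70, SDs 1.7 and 1.39, alpha 0.05, power 95% and loss 20% are from section 2.7. Sidedness is not stated; two-sided is assumed.

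**Reproducing the plan's figure.**

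- Difference: 3.70 − 2.37 = 1.33 (absolute value).
- Pooled SD: √((1.7² + 1.39²)/2) = 1.553.
- Standardised difference: d = 1.33/1.553 = 0.857.
- Normal approximation: n = 2(1.960 + 1.645)²/0.857² ≈ 35.4, so 36 per arm.
- Allowing for loss: 36/(1 − 0.20) = 45 per arm, as stated.

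Power at 36 completers per arm is 95.3% by the normal approximation and 94.8% by the noncentral t. A one-sided test does not reproduce the figure (31 per arm, 39 after loss).

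**If the values are changes with the arms transposed.** The SDs are already SDs of change, d = 0.857 applies to the declared endpoint, and the power stands.

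**If the values are week-8 scores.** Randomised arms share the same expected baseline, so the expected difference in change is still 1.33. Only the SD alters. With equal SDs at baseline and follow-up (an assumption) and correlation rho:

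- SD of change = 1.553 × √(2(1 − rho))
- d for the change score = 0.857/√(2(1 − rho))
- d for the baseline-adjusted follow-up score = 0.857/√(1 − rho²)

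Power is by the two-sided noncentral t at 36 completers per arm. The last column is the number per arm for 95% power with the change score, after division by 0.8.

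| rho | SD of change | Power, change score | Power, baseline-adjusted | Per arm needed, change score |
|---|---|---|---|---|
| 0 | 2.196 | 71.7% | 94.8% | 90 |
| 0.1 | 2.083 | 76.2% | 95.0% | 82 |
| 0.2 | 1.964 | 80.9% | 95.5% | 73 |
| 0.3 | 1.837 | 85.7% | 96.4% | 64 |
| 0.4 | 1.701 | 90.5% | 97.4% | 55 |
| 0.5 | 1.553 | 94.8% | 98.5% | 47 |
| 0.6 | 1.389 | 98.0% | 99.4% | 38 |
| 0.7 | 1.203 | 99.6% | 99.9% | 29 |

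At rho = 0.5 the SD of change equals the SD of the score, so the stated power is kept at about 0.5 and above and lost below it.

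**Units.** If the source used a 0-10 scale, 1.33 is 13.3 mm on the protocol's 100 mm line. The protocol does not state the source's scale.

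**The case against.** The strongest reply is that the sample size reproduces and that a shortfall needs two things the protocol does not establish: that the values are scores, and that rho is below about 0.5. This stands. A reader might infer that the trial is underpowered or that the 95% is wrong. The document does not support that. Section 2.7 literally says change, and if the arms were swapped in writing the SD objection disappears. It would also disappear if the figures were signed changes from baseline, but pain would then have risen in both arms of the source trial.

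The table also leans cautious in two respects.

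- The loss of 20% is a ceiling. With all 45 per arm, equal SDs and rho 0.4, change-score power is 95.6% rather than 90.5%.
- Entry requires VAS above 40 mm, which may make the baseline SD smaller. The break-even correlation is then SD(baseline)/(2 × SD(follow-up)). With an assumed baseline SD of 1.2, power at 36 per arm is about 92% at rho 0.3 and 95.2% at rho 0.4. The same restriction may also lower rho, so this shows sensitivity and does not prove that power is adequate.

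A reader might also infer that loss was allowed for in the wrong way, because the noncentral t gives 37 per arm and 37 × 1.2 = 44.4, which rounds up to 45. The protocol shows no such step, and 36/0.8 gives 45 exactly, so there is no ground for that criticism.

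Finally, the Discussion already warns that the basis of the sample size is uncertain. It does so for other reasons, so it does not answer this point.

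**Conclusion.** The planning values are mislabelled or reversed as printed, and nothing else in the article settles which. That much rests on the text alone.

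The power consequence is conditional. If the values are week-8 scores, the 95% is not established for a change-score comparison, which is different from being refuted: power runs from about 72% at rho 0 to over 99% at rho 0.7. This rests on equal SDs, 36 completers per arm, a two-sided test and a true difference of 1.33. If the arms are transposed, the stated power holds. The figure of 45 per group is arithmetically sound on either reading, and no increase in sample size follows from this point.

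**What to change.** Check the cited source and rewrite the paragraph in section 2.7:

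- State whether 2.37 and 3.70 are scores or changes, in which arm order, and on what scale (1.33 = 13.3 mm if 0-10).
- Name the quantity that is powered.
- If they are changes with the arms transposed, correct the order; the power statement can stay.
- If they are scores, choose one of two routes. Either restate power for the change score at 36 per arm, giving the assumed rho or an SD of change with a range. Or make the baseline-adjusted week-24 VAS the powered analysis, which gives about 95% or more at 36 per arm with the planned 90.

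The cost is one paragraph and no added patients. The second route also requires the baseline-adjusted comparison to be named in section 2.21, before the group codes are opened. The downside is that the stated power may become less favourable if the unadjusted change-score test is kept.

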### Random

2.8

After the baseline assessment, eligible participants will be randomly assigned to the intervention group or the control group. The random allocation sequence will be generated using the planning program of the statistical software Statistical Analysis System (SAS V.9.0) (SAS Institute Inc., Cary, NC, USA) and managed by an independent research assistant. Will be responsible for randomly assigning sequences and blind codes. The subject's work result (intervention group or control group) will be replaced with the letter “A” or “B” in the first blind code, and the true value of “A” or “B” will be set in the second blind code. meaning. After locking the database, the independent research assistant will move to the statistician through the participant's group code “A” or “B”, and declare it as the “A” or “B” group after completing all data analysis.

### Blinding

2.9

In this trial, since the focus of the trial is non-pharmacological intervention, it is impossible to blind the participants and physicians, but use blinding for evaluators and statisticians.

### Intervention

2.10

If necessary, all participants will continue to receive conventional medical treatment or rehabilitation. Conventional medical treatment or rehabilitation will be based on the Chinese association for the study of pain chronic non-specific low back pain Assessment and Management Consensus (2019).^[31]^ At the same time, all participants will receive the same health education during the intervention period. Participants in the intervention group will receive Baduanjin exercise, while participants in the control group will be told to maintain their usual lifestyle.

### Study schedule

2.11

The research schedule is listed (Fig. 2). The trial will include a screening phase, an intervention phase and a follow-up phase. During the screening phase, participants sign informed consent. Researchers will obtain basic demographic information and use VAS to determine whether participants are eligible for clinical trials. If participants are undergoing rehabilitation training or exercise therapy, we will implement a 2-week flushing period. During the 24- week treatment period, the 2 groups of patients were measured before the intervention, at 8, 16, and 24 weeks after the last training session of the week. In the intervention group, Baduanjin training was performed 3 times a week. The follow-up survey of the intervention group will be conducted 4 weeks after the last training, and the control group will be conducted at the 28th week.

